# Optimising the Intervention

The chosen approach is action research (AR). For those not familiar with this method, it is a cyclical process of plan, act, reflect and learn, and adapt the planned activities to enhance the final outcome of what we endeavour to achieve 10. It is broader than a ‘plan do study act’ quality improvement cycle. Its mixed heritage includes anthropological campaigns that sought to challenge social structures by using research understanding to empower the least powerful in society. More pragmatically, the processes have proven useful to iteratively clarify the requirements and concerns of those involved in deploying or using new technologies.

Action research implies cycles and iterations of learning and application 10 11. For the ASSET project action research will be used as follows:

- The current project defined as the exploration of telemonitoring in New Zealand, and as formative pilot study for future randomised clinical trials on telemonitoring, is the primary and encompassing AR cycle, and
- Each three month allocation of telemonitoring for a patient will be considered a cycle of planning, acting and learning.

AR also implies that a problem has been identified, is being clarified and resolved 10. For three DHBs the clinicians and healthcare service providers have identified a chronic condition management issue that telemonitoring could contribute to with positive outcomes, while Tairawhiti DHB has a different approach. The Tairawhiti community will be invited to participate with clinicians and service providers to identify the problem/s for which telemonitoring could contribute a solution.

More specifically, the researchers will:

- observe those using the technologies, primarily the clinical nurse specialists, patients / whanau, each for about 4 periods of one hour over 3 months
- conduct semi-structured interviews with each at the beginning and end of the intervention
- iteratively review their findings with each party at the end of each observation period
- record changes they observe as the intervention is refined
- seek to establish and document consensus on an algorithm of care the CNS will use for a further trial

# Describing usual care

The researchers will use an observation and interviews, as above, to decribe and document ‘usual care’ at each site.

As part of this process we will ask each CNS to keep a diary of costs and resource use for 1 month, and each patient/whanau participants to keep a diary of costs and resource use for 2 weeks.

In addition, each patient in the usual care group will be asked to complete the same interview and questionnaire schedule as the Intervention group, less the technology-specific components.

# Outcome Measures

*Primary Scales*

1. HRQoL measured using the 36-item Short Form (SF-36) questionnaire

2. Self-efficacy measured on scale Self-Efficacy for Managing Chronic Disease 6-item scale

3. Disease-specific scales

a. COPD - St George Respiratory Questionnaire12; BODE Index13; COPD Helplessness Scale14

b. CHF – Minnesota Living with Heart Failure Questionnaire15

c. Other conditions -

*Primary quantitative health outcomes and resource use*

Hospital ED attendance, admissions, length of stay - all cause and disease-specific

*Secondary* – physical function, number and length of admissions to acute hospitals as well as time between initial and subsequent admission, number of GP consultations, quantity and quality of social support networks, and adverse events (falls and other injuries) and sense of control in chronic care consumer; HRQoL and mental wellbeing in carer or family (whänau); adoption of self management programme; adoption of telecare equipment and associated processes and workflow changes by participants, including organisational impact, e.g. changes in ASH rates, satisfaction with services.

*Financial* – Direct and indirect economic costs in the consumer, caregiver or family (whänau), and health service provider. Cost data will be collected for both intervention and control group costs for attending hospital. Technology costs for the intervention group only. Financial benefits will be calculated by the difference in admission and treatment costs between the two groups. Costs will be calculated using the ongoing cost of monitoring and interventions. The net cost savings or benefit will allow the return on investment to be calculated.

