# Study Design

ASSET will be conducted as:

- **Three separate randomised controlled trials** in Auckland, Counties Manukau and Canterbury (there will be no control group in Tairawhiti)
- Within each of the active intervention arms, including Tairawhiti, there will be an **action research process to optimise the telecare system intervention.**
- Within each control arm there will be a **process of mapping real usual care.**

Each region will stand alone as a discrete trial though with some shared outcomes. Standard criteria and measures will apply across all trials.

The telecare equipment will be available to all four health services for 12 months, with equipment loaned to any one patient for up to three months.

Participants will be assessed at baseline with follow up at three (immediately post intervention) and six months (three months post intervention).

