# Eligibility

**Inclusion criteria:**

1. *All areas*
   1. age 16+
   2. living permanently at home
   3. expected to be available for 3 months
   4. expected to survive study period
   5. able to communicate in English (or someone in household able to translate)
   6. able to physically manage the equipment (or someone available to assist)
2. A*uckland* – Permanently resides in the Auckland DHB region, current or recent in-patient to Auckland City Hospital with heart failure as the primary reason for admission
3. *Counties Manukau* – Permanently resides in the Counties Manukau DHB region, enrolled with ProCare PHO, current or recent in-patient at Middlemore Hospital with COPD as the primary reason for admission
4. *Tairawhiti* – Permanently resides in the Tolaga Bay area, enrolled with Ngati Porou Hauora PHO, and is on the PHO chronic condition management programme
5. *Canterbury* – Permanently resides in the Canterbury DHB region, enrolled with practices working with the community specialist respiratory service, with COPD being treated with Long Term Oxygen Therapy (LTOT) at home

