**Recruitment strategies:**

*Auckland* – identified by CNS on admission with CHF, screened for eligibility and consent to pass name to researcher, who will conduct formal consent process.

Counties Manukau - identified by CNS on admission with COPD, screened for eligibility and consent to pass name to researcher, who will conduct formal consent process.

Tairawhiti – identified by chronic care nurse, from current register of community patients, she will screen for eligibility and conduct formal consent process.

Canterbury - identified by CNS on admission with COPD, screened for eligibility and consent to pass name to researcher, who will conduct formal consent process.

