# Randomisation and study group assignment

Immediately after baseline data collection, participants in Auckland and Counties Manukau will be randomised to intervention or control arms. The researcher will phone an Interactive Voice Response (IVR) system via an 0800 number, provide basic patient identification data and be assigned a study group for that patient.**

*Eligible  consent  baseline data collection  individual randomly assigned to intervention or control*

In Christchurch, a pre-assigned cluster randomisation will assign participating general practice surgeries – and the patients attending them – to intervention or control arms of the study.

*Eligible  consent  baseline data collection  cluster randomised to intervention or control, based on randomly assigned group of patient’s general practice*

In Tairawhiti, patients will not be assigned to separate groups.

*Eligible  consent  baseline data collection  followed in telecare programme*

Note: initially we intended to randomise with stratification by age / gender / distance from hospital / ethnicity. We have decided against this as i) we are collecting pilot data and will find if we obtain an adequate stratification by including all who are eligible and consent ii) there are technical and efficiency reasons not to stratify. From this pilot data we will be better informed as to whether stratification will be necessary in a follow up trial.

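### The secondary outcome of time between admissions has no consistent or sound time origin, and analysed as completed intervals it would hide most of a true delay

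*Protocol*

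**What the plan says.** In the protocol's Outcome Measures section, one item in the list of secondary outcomes is "time between initial and subsequent admission". Neither admission is defined there, and the interval does not appear in the Appendix 2 table of outcomes.

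Whether patients have an admission at entry depends on the region:

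- **Auckland** (Inclusion criteria): "current or recent in-patient to Auckland City Hospital with heart failure as the primary reason for admission".
- **Counties Manukau** (Inclusion criteria): "current or recent in-patient at Middlemore Hospital with COPD as the primary reason for admission". Neither region puts a limit on 'recent'.
- **Canterbury**: the inclusion criterion is "with COPD being treated with Long Term Oxygen Therapy (LTOT) at home", with no admission needed. The Recruitment strategies section says "Canterbury - identified by CNS on admission with COPD, screened for eligibility and consent to pass name to researcher".
- **Tairawhiti**: patients are "identified by chronic care nurse, from current register of community patients", and the Study Design section says "there will be no control group in Tairawhiti".

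On timing, the randomisation section says "Immediately after baseline data collection, participants in Auckland and Counties Manukau will be randomised to intervention or control arms". In Canterbury, general practices are assigned to an arm beforehand, and a patient takes the arm of his or her practice.

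The Analysis section assigns mixed-effects models to continuous variables and negative binomial regression to counts, rules out imputation, and names no time-to-event method.

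**The concern.** An interval between two admissions needs a starting admission. There are two candidates, and each has a problem.

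If the start is the qualifying admission, the clock runs before allocation. The interval then contains a stretch of unknown length in which the patient belonged to neither arm. A patient readmitted during that stretch would already have the outcome before randomisation.

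If the start is the first admission after entry, the outcome exists only for patients who have had the event that the second research hypothesis says telecare will reduce. The arms then contribute differently selected patients, and the delay of most interest, the one before that first admission, is left out.

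On either choice, if the interval is treated as a continuous variable with no imputation, only patients with both admissions contribute. Fixed follow-up cuts off the long intervals in both arms, so a real delay could be reported as almost none.

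**Working it through.** **The plan's own figure.** There is none to reproduce. The protocol gives no admission rate, effect size or power for this outcome.

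**Inputs**
- From the protocol: 6 months to the last assessment (Study Design); 1 year for counting admissions (Appendix 2); 48 intervention patients per randomised region (Appendix 8).
- Assumed: constant admission rates λ of 1.0 per patient-year under usual care and 0.7 with telecare (a 30% reduction), no deaths, 365.25 days per year. A second setting uses 2.0 versus 1.4.

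**Formulas**, with follow-up T and x = λT:
- Share admitted at least once: P1 = 1 − e^(−x)
- Share with two admissions: P2 = 1 − e^(−x)(1 + x)
- Mean completed gap, first to second admission: (1/λ) × P3/P2, where P3 = 1 − e^(−x)(1 + x + x²/2)
- Mean time to first admission among those admitted: 1/λ − T e^(−x)/P1
- Mean admission-free time in all patients, up to T: P1/λ

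**Results at T = 0.5 year** (x = 0.50 and 0.35; e^(−x) = 0.6065 and 0.7047)

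| Quantity | Usual care | Telecare | Difference |
|---|---|---|---|
| Two admissions after entry | 9.0% | 4.9% | |
| Of 48 patients | 4.3 | 2.3 | |
| Mean completed gap, first to second (days) | 58.3 | 59.1 | 0.8 |
| Mean time to first admission, admitted patients only (days) | 83.7 | 86.0 | 2.3 |
| Admitted at least once | 39.3% | 29.5% | |
| Admission-free time, all patients (days) | 143.7 | 154.1 | 10.4 |

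For example, usual-care admission-free time is 0.3935/1.0 × 365.25 = 143.7 days, and telecare is 0.2953/0.7 × 365.25 = 154.1 days. Starting at the qualifying admission adds the same expected lag to both arms, so the 2.3-day difference among readmitted patients does not grow.

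**Sensitivity**
- T = 1 year, rates 1.0 versus 0.7: 26.4% versus 15.6% have two admissions. The completed gap is 111.0 versus 114.3 days (3.3), time to first admission among those admitted 152.7 versus 161.5 days (8.8), and admission-free time 230.9 versus 262.7 days (31.8). The direction is the same.
- T = 0.5 year, rates 2.0 versus 1.4: completed gap 55.5 versus 57.2 days (1.7); admission-free time 115.4 versus 131.3 days (15.9).

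**Does the earlier start bias a censored analysis?** This was simulated with 100,000 patients per arm, a Cox model, a true hazard ratio of 0.7, and a mean lag of 1 or 8 weeks from qualifying admission to randomisation. The lag had the same distribution in both arms and contained no readmission. Follow-up was 6 months.

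| Analysis with censoring | No variation between patients | Gamma frailty, variance 1 |
|---|---|---|
| Clock from randomisation | 0.70 | 0.74 |
| Clock from qualifying admission | 0.70 | 0.74 |
| First-to-second gap, effect persists | 0.69–0.71 | 0.74 |
| First-to-second gap, only first admission delayed | 0.98–0.99 | 1.00–1.04 |

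The earlier start does no material harm to a censored comparison. The first-to-second gap misses a delay confined to the first admission. With frailty, 33% of usual-care but 26% of telecare patients enter that analysis.

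**The case against.** The strongest reply has four parts.

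1. **The natural reading is sound.** Patients in Auckland and Counties Manukau enter through an admission, so the initial admission is most naturally that one. Allocation follows it, so the lag is balanced by randomisation. This stands for a censored analysis, as the hazard ratios show. A reader might infer that the outcome cannot show a delay at all; that goes too far. It might also seem that patients must stay out of hospital until randomisation. Nothing in the eligibility criteria says so, which is why a readmission before allocation could be counted.

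2. **Canterbury does have an index admission, and Tairawhiti loses nothing.** A reader of the inclusion criteria alone might conclude that Canterbury has no starting event. The recruitment strategy contradicts that, so the finding there is a conflict between two sections. Tairawhiti has no index admission but also no control group, so no randomised contrast is lost.

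3. **The benefit would be seen elsewhere.** Admissions are a primary outcome, modelled as counts with an exposure term, and the protocol says the study is not powered for most outcomes. This stands and limits the weight of the point.

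4. **Time origin and censoring belong in the SAP.** In part. Censoring rules can wait for the SAP. But the protocol itself fixes the outcome as an interval between two admissions, and its Analysis section offers only continuous and count models without imputation. That choice leads towards completed intervals, and a SAP faithful to the wording would inherit it.

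The calculations rest on assumed rates, and they ignore deaths although the protocol expects about 20% per year in COPD and heart failure.

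**Conclusion.** The point holds, at moderate weight for one of many secondary outcomes in a pilot. The outcome has no consistent time origin across the randomised regions. One reading counts time before allocation; the other selects patients by a post-randomisation event. If completed intervals are analysed, a 30% rate reduction worth about 10 days of admission-free time over 6 months shows as about 1 to 2 days. Over 1 year the figures are about 32 days against 3 to 9.

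The sizes depend on the assumed constant rates and effect. The loss from dropping patients without both admissions appeared in every setting tried. With censoring, time from the qualifying admission remains a valid comparison where individuals are randomised.

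**What to change.** In Outcome Measures, replace the item with time from randomisation to first subsequent hospital admission, all-cause and disease-specific. In Canterbury, where practices are pre-assigned and there is no randomisation date per patient, start at patient enrolment.

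- Do not count the qualifying stay. For patients still in hospital, keep the clock at randomisation or enrolment; restarting it at discharge would create a new post-randomisation origin.
- Censor patients without an admission at the end of follow-up, and state whether that is 6 months or 1 year.
- Treat death as a competing or composite event.
- In the Analysis section, name a time-to-event method, allowing for clustering by practice in Canterbury.
- Restrict to unplanned admissions only if the DHB data identify them in both arms. The adverse event section records unplanned hospitalisation for the intervention group only.
- Reconcile the Canterbury inclusion criterion with the Canterbury recruitment strategy.

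The cost is a few lines of text and slightly more analysis work on a secondary outcome. Appendix 2 already takes admissions from the DHB database, so little or no new data collection should be needed.

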# Adverse event reporting

All of the people enrolled in this study are under ‘usual care’ – from their general practitioner and / or hospital specialists - with or without the addition of telecare. Given that the participants are either unwell or may become unwell, possibly at short notice, we must allow for the possibility that introducing telecare may disrupt care in ways not anticipated.

Adverse events to be recorded and assessed by independent review, for intervention group only, within 6 months of enrolling in study:

1. Death
2. Unplanned hospitalisation or prolongation of hospitalisation
3. Patient withdraws from study

A **Data and Safety Monitoring Board Panel** (DSMP) will be appointed to undertake and / or oversee these reviews. The Panel will include clinical, research and statistical skills. Analyses will be un-blinded.

See **Appendix 2** for adjudication process and reporting

# Data Handling and Record Keeping

****[name]**

**Confidentiality**

Information about study participants will be kept confidential and managed according to the requirements of The Code of Health and Disability Services Consumers' Rights, 1996, and the Ethics approval specific to this study.

**Source Documents**

Source data is all information, original records of clinical findings, observations, or other activities in a clinical trial necessary for the reconstruction and evaluation of the trial. Source data are contained in source documents. Examples of these original documents and data records include: hospital records, clinical and office charts, completed interview schedules, and subject files involved in the clinical trial.

**Case Report Forms**

The study case report form (CRF) is the primary data collection instrument for the study. All data requested on the CRF must be recorded. All missing data must be explained. If a space on the CRF is left blank because the procedure was not done or the question was not asked, write “N/D”. If the item is not applicable to the individual case, write “N/A”. All entries should be printed legibly in black ink. If any entry error has been made, to correct such an error, draw a single straight line through the incorrect entry and enter the correct data above it. All such changes must be initialled and dated. **Do not erase or white-out errors.** For clarification of illegible or uncertain entries, print the clarification above the item, then initial and date it.

**Records Retention**

It is the local researcher’s responsibility to retain study essential documents and deliver these to the Study Manager at the cessation of the study. The Study Manager will ensure these records are retained securely for a period of 10 years from collection, or otherwise as indicated in the Ethnics approval specific to this study.

**Data and document handling**

The following table outlines the flow of information from recruitment to assessment.

Table 1: summary of data and document handling

| **Record** | **Data handling procedure** |  |
| --- | --- | --- |
| Eligible clients list | Stored electronically by local researcher; emailed to Study Manager weekly |  |
| Ineligible clients list | Stored electronically by local researcher; emailed to Study Manager weekly |  |
| Contact list | Stored electronically by local researcher; emailed to Study Manager weekly |  |
| Declined clients list | Stored electronically by local researcher; emailed to Study Manager weekly |  |
| Delayed Interview list | Stored electronically by local researcher; emailed to Study Manager weekly |  |
| Randomisation list | Auckland and Counties Manukau: researcher phones randomization service while still with patient, records on Care Report Form, updates local list of Intervention and Control patients, emails Study Manager within 24 hours.  Canterbury: researcher confirms general practice of patient, confirms and records Intervention or Control group, emails Study Manager within 24 hours. |  |
| Enrolled participant list | Local researcher maintains up-to-date list; emails to Study Manager weekly |  |
| Participant contact card | Local researcher maintains up-to-date list; emails to Study Manager weekly |  |
| Withdrawn participant list | Local researcher maintains up-to-date list; emails to Study Manager weekly |  |
| Participant research interview (CRF = Case Report Form) | Local researcher keeps original, faxes or emails Study Manager weekly. Transfers originals to Study Manager at end of study. |  |
| Interview recordings | Digital recording and field notes sent to Study Manager within 24 hours. |  |

# Statistical Issues

**Potential patients available and recruitment rate**

We estimate that about two thirds of those invited to participate will consent, about 20% will drop out. In addition, for COPD and heart failure, we estimate that the death rate will be about 20% per year.

**Sample size**

Each region will be a stand-alone and discrete trial though with some shared outcomes. Standard criteria and measures will apply across all trials. A sample size of 120 within Auckland, Counties Manukau and Canterbury will provide a power of 90% with alpha = 0.05 to detect a 10 point increase in SF36. Similarly, the literature (Bourbeau) suggests we need 86 patients in each study arm to have 90% power (alpha 0.05) to detect a mean change of 4 (the minimum important difference) on the St George Respiratory Questionnaire. Detecting some other outcomes will require more patients.

See separate document, “ASSET planning and power calculations” for details of data underlying power calculations.

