# Appendix 8. Workload and equipment needed by month

| **Auckland** |  |  |  |  |  |  |  |  |  |  |  |  |  |  |  |  |  |  |
| --- | --- | --- | --- | --- | --- | --- | --- | --- | --- | --- | --- | --- | --- | --- | --- | --- | --- | --- |
|  |  |  |  |  |  |  |  |  |  |  |  |  |  |  |  |  |  |  |
| Patient numbers in active and control arm, with tallies for clinical load, equipment numbers, researcher load | | | | | | | | |  |  |  |  |  |  |  |  |  |  |
| **equipment used 4 times, 3 months per patient** | | |  |  |  |  |  |  |  |  |  |  |  |  |  |  |  |  |
| recycle equipment starts Jun 10 | |  |  |  |  |  |  |  |  |  |  |  |  |  |  |  |  |  |
|  |  |  |  |  |  |  |  |  |  |  |  |  |  |  |  |  |  |  |
|  | **Mar-10** | **Apr-10** | **May-10** | **Jun-10** | **Jul-10** | **Aug-10** | **Sep-10** | **Oct-10** | **Nov-10** | **Dec-10** | **Jan-11** | **Feb-11** | **Mar-11** | **Apr-11** | **May-11** | **Jun-11** | **Jul-11** | **Aug-11** |
| **Clinical load** |  |  |  |  |  |  |  |  |  |  |  |  |  |  |  |  |  |  |
| recruitment total | 8 | 8 | 8 | 8 | 8 | 8 | 8 | 8 | 8 | 8 | 8 | 8 |  |  |  |  |  |  |
| recruitment to intervention | 4 | 4 | 4 | 4 | 4 | 4 | 4 | 4 | 4 | 4 | 4 | 4 |  |  |  |  |  |  |
| intervention total current | 4 | 8 | 12 | 12 | 12 | 12 | 12 | 12 | 12 | 12 | 12 | 12 | 8 | 4 |  |  |  |  |
|  |  |  |  |  |  |  |  |  |  |  |  |  |  |  |  |  |  |  |
| **Equipment load** |  |  |  |  |  |  |  |  |  |  |  |  |  |  |  |  |  |  |
| equipment in use | 4 | 8 | 12 | 12 | 12 | 12 | 12 | 12 | 12 | 12 | 12 | 12 | 8 | 4 |  |  |  |  |
|  |  |  |  |  |  |  |  |  |  |  |  |  |  |  |  |  |  |  |
| **Researcher load** |  |  |  |  |  |  |  |  |  |  |  |  |  |  |  |  |  |  |
| new patient training | 4 | 4 | 4 | 4 | 4 | 4 | 4 | 4 | 4 | 4 | 4 | 4 |  |  |  |  |  |  |
| patient baseline assessment | 8 | 8 | 8 | 8 | 8 | 8 | 8 | 8 | 8 | 8 | 8 | 8 |  |  |  |  |  |  |
| patient 3 month assessment |  |  |  | 8 | 8 | 8 | 8 | 8 | 8 | 8 | 8 | 8 | 8 | 8 | 8 |  |  |  |
| patient 6 month assessment |  |  |  |  |  |  | 8 | 8 | 8 | 8 | 8 | 8 | 8 | 8 | 8 | 8 | 8 | 8 |
| total assessments + training | 12 | 12 | 12 | 20 | 20 | 20 | 28 | 28 | 28 | 28 | 28 | 28 | 16 | 16 | 16 | 8 | 8 | 8 |
|  |  |  |  |  |  |  |  |  |  |  |  |  |  |  |  |  |  |  |
| **Total patients experiencing telecare system** | | | **48** |  |  |  |  |  |  |  |  |  |  |  |  |  |  |  |

| **Counties** |  |  |  |  |  |  |  |  |  |  |  |  |  |  |  |  |  |  |

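### The sample-size section claims 90% power for the SF-36 from 120 patients per site, but Appendix 8 recruits 96 per site and carries all of them to 6 months despite the expected losses

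*Protocol*

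**What the plan says.** The Sample size section of the protocol fixes the unit of inference: "Each region will be a stand-alone and discrete trial though with some shared outcomes". It then states that "A sample size of 120 within Auckland, Counties Manukau and Canterbury will provide a power of 90% with alpha = 0.05"; the target is a 10-point difference on the SF-36. It does not say whether 120 is a site total or a number per arm, or whether it counts patients recruited or patients evaluable. For the St George Respiratory Questionnaire (SGRQ) it cites the literature as showing that "we need 86 patients in each study arm to have 90% power" for a mean change of 4. The SDs are left to a separate power-calculation document.

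The section just before it, on available patients and recruitment rate, expects that "about two thirds of those invited to participate will consent, about 20% will drop out". For COPD and heart failure it adds deaths of about 20% per year.

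Appendix 8 gives the same figures for Auckland, Counties Manukau and Canterbury: 8 recruits a month for 12 months, 4 of them to telecare. The row "Total patients experiencing telecare system" reads 48 at each of these sites. Baseline, 3-month and 6-month assessments each run at 8 a month for 12 months.

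**The concern.** The recruitment plan is smaller than the number on which the power statement rests, and nothing in the text shown connects the two. Neither the Sample size section nor Appendix 8 shows an allowance for the losses that the protocol itself predicts. The Analysis section rules out imputation, so those losses reduce the data available.

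The SF-36 is the first-listed primary scale, and each region is to stand alone. A null SF-36 result at one site could be read as if the trial had 90% power to find 10 points. The study is also meant to supply planning figures for later trials, so its assumptions on retention and precision need to be right.

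**Working it through.** **Step 1. Counts, with no assumption needed.**
- Recruited per site: 8 × 12 = 96. To telecare: 4 × 12 = 48, leaving 48 controls.
- Against 120 per site: 120 − 96 = 24 short, and 24/120 = 20%.
- Six-month assessments scheduled: 8 × 12 = 96, so no loss is applied.

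**Step 2. Expected losses.**
- After 20% drop-out: 96 × 0.80 = 76.8 (38.4 per arm).
- Deaths at 20% per year are about 10% over 6 months: 76.8 × 0.90 = 69.1 (34.56 per arm).
- This assumes that all the drop-out has occurred by 6 months.

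**Step 3. The plan's own figure.** The 120 cannot be reproduced because the protocol gives no SD. The SD that makes it exact can be solved for. For two equal arms, two-sided alpha 0.05 (sidedness is not stated) and 90% power:

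SD = δ√(n/2) / (1.960 + 1.282)

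With n = 60 per arm and δ = 10: 10 × √30 / 3.242 = 16.9. The noncentral t gives 16.8.

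**Step 4. Power at the Appendix 8 numbers.** Power = Φ(δ / (SD√(2/n)) − 1.960). For n = 48 and SD 16.9: 10 / (16.9 × √(2/48)) = 2.899, and Φ(0.939) = 0.826. The table gives the noncentral-t result, with this normal approximation in brackets.

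| Reading of 120 | Implied SD | 48 per arm, no loss | 38.4 per arm, drop-out | 34.56 per arm, drop-out and deaths |
|---|---|---|---|---|
| Evaluable site total (60 per arm) | 16.8 (16.9) | 82.5% (82.6%) | 73.3% (73.7%) | 68.6% (69.2%) |
| Recruited site total, 20% drop-out included (120 × 0.8 = 96 evaluable) | 15.0 (15.1) | 90.0% (90.0%) | 82.4% (82.6%) | 78.2% (78.5%) |
| Per arm | 23.8 (23.9) | 53.1% (53.6%) | 44.3% (45.0%) | 40.6% (41.3%) |

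On the first reading, a one-sided test (normal approximation) gives 83.5%, 75.7% and 71.8%.

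**Step 5. Detectable difference, first reading.** With 90% power this is 3.242 × SD × √(2/n). At 48 per arm: 3.242 × 16.9 × 0.204 = 11.2 points. At 34.56 per arm: 3.242 × 16.9 × 0.241 = 13.2 (13.3 by noncentral t). The plan states 10.

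**Step 6. Canterbury.** This site randomises general practices, and no design effect is shown. As an illustration only, assume 4 to 12 patients per practice and an intracluster correlation of 0.01 to 0.05. The design effect 1 + (m − 1) × ICC then runs from 1.03 to 1.55. SF-36 power at 48 per arm, before losses, falls to between 82% and 64% (SD 16.9, normal approximation).

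**Step 7. SGRQ.** 48 against 86 per arm is (86 − 48)/86 = 44% short. The SD implied by 86 per arm is about 8.05, which gives about 67% power at 48 per arm. This concerns Counties Manukau and Canterbury only, because Auckland is a heart-failure site.

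**The case against.** **The study is a pilot.** The protocol says under Terminology that it is not powered to confirm effectiveness for most outcomes, and it leaves definitive testing to later studies. This softens the consequence. But the same sentence refers the reader to the power calculations, and those still claim 90% for the SF-36.

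**120 may already include drop-out.** 120 × 0.8 is exactly 96, so it cannot be asserted that losses were ignored when 120 was chosen. This does not rescue the plan, because Appendix 8 labels the 96 as recruitment and baseline assessments, so losses come off that number. It is fair to add that Appendix 8 is a workload table, and its full follow-up rows may be staffing ceilings.

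**The SD is unknown.** A reader might infer that no site can have the stated power. The document does not prove that: with an SD of 15, 48 evaluable per arm gives about 90%. What is established is that the stated number and the planned number differ.

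**The planned analysis is not a completers' t-test.** The Analysis section specifies mixed-effects models with a group-by-time interaction. Patients lost after 3 months still contribute, so the figures after losses are illustrations. The recruitment shortfall is unaffected.

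**120 might be pooled over the three sites.** Site is a fixed effect in the analysis model, and 3 × 96 = 288 exceeds 120. But the power sentence directly follows the declaration that each region stands alone.

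**Two stronger readings fail.** A reader might infer that the protocol claims 90% power for the SGRQ. It gives 86 per arm as a requirement from the literature and does not say that it is met.

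A reader might also infer that 48 telecare patients cannot be served, since "The telecare equipment will be available to all four health services for 12 months" while Appendix 8 shows kits in use for 14 months (Auckland, Counties Manukau) or 17 months (Canterbury). The in-use rows do not support this. They sum to 144 = 12 kits × 12 months at the first two sites and 288 = 24 kits × 12 months at Canterbury. The longer spans are staggered 12-month kits, and 12 × 4 and 24 × 2 both give 48 loans.

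**Conclusion.** The point holds for the SF-36 at all three randomised sites. The power statement rests on 120 per stand-alone trial, while the recruitment plan delivers 96, with no visible allowance for the predicted losses. That conflict is plain arithmetic, given that 120 applies to each site.

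The effect on power depends on what 120 means and on SDs back-solved from the plan's own claim. On the most natural reading, an evaluable site total, power is about 82% before losses and 69 to 73% after. The most favourable site-level reading gives 90% with no loss and about 78 to 82% with losses. The per-arm reading gives about 53% before losses. These values assume a two-sided test, a simple two-group comparison and individual randomisation. They show the size of the problem and should not be written into the protocol as its power.

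For the SGRQ the criticism is limited: 48 per arm is well below the cited 86, and the section should say so.

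**What to change.** In the Sample size section:
1. State whether 120 is per site or per arm, and whether it is recruited or evaluable.
2. Reconcile it with the 96 in Appendix 8, by correcting one or the other.
3. If 96 stands, restate the SF-36 power for 96 recruited less the stated drop-out and deaths. For a pilot, the detectable difference and the confidence-interval half-width would serve better. Take the SD from the power-calculation document, name the SF-36 score to which it applies, and include a design effect for Canterbury.
4. Say that the 86 per arm for the SGRQ is not reached at the two COPD sites.

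This is a change of wording and needs no extra patients. Its cost is a less favourable stated power. If 120 evaluable per site is to be kept instead, recruitment would have to rise to 120/0.80 = 150 per site for drop-out alone, or 120/0.72 = 167 with 6-month deaths, and Appendix 8 would need new recruitment rows.
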